### Patient recruitment, consent, allocation

Patients will be recruited from 10 GP practices and their associated physiotherapy services within the Waterford City Primary Care area. The Waterford City Primary Care area serves a population of approx 47,000 people [26]. Potential patients will be identified (based on the inclusion criteria) when they consult their GP practice or primary care physiotherapy team and subsequently will be referred to the Back Pain Clinic at Waterford Regional Hospital. On receipt of the referral, the Back Pain clinic will forward an appointment to the patient, in addition to a copy of the self report baseline questionnaires as per usual care and written information regarding the study. On the initial screening day, the ‘STarT Back’ screening tool will be administered and patients stratified according to their level of risk of persisting symptoms - low, medium or high risk. Patients will be assessed as routine care. Routine care will include history taking, a physical examination, review of completed self report questionnaires and performance of timed functional outcome measures. Following the clinical assessment, if patients are deemed suitable for the study, a full explanation will be given by the principle investigator and any patient concerns addressed. If the patient is then willing to participate, written consent will be obtained (Figure 1).

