**Figure 1 F1:**
[figure not shown]
Study flow chart.

The historical control consists of patients who attended the Back Pain Clinic between 2009–2011. These patients were referred from the 10 GP practices and their associated physiotherapy services within the Waterford City Primary Care area in exactly the same manner as the intervention group. The patients completed a copy of the same self report questionnaires as the intervention group. In the control group, risk stratification was performed by an independent party (administrator at the clinic) after the initial assessment using the STarT Back scoring algorithm. The therapists were blinded as to the risk stratification of each patient until completion of the treatment intervention at three months. Patients in the historical control group were assessed as routine care which included history taking, a physical examination, review of completed self report questionnaires and performance of timed functional outcome measures in exactly the same manner as the intervention group. Following initial assessment if patients were deemed suitable, all patients irrespective of their risk stratification were entered into a generic 12 week group exercise/education intervention. Consent was obtained retrospectively for the inclusion of these historical controls in line with the National Consent Policy [27].

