**Exclusion**	
Pathology	Suspected or confirmed serious spinal pathology (cauda equine syndrome, fracture, metastatic, inflammatory spinal disease, pre-existing neurological condition)
Past medical history	Illicit drug use, spinal surgery, spinal cord stimulator implantation, cardiac history, psychiatric illness or personality disorder, intellectual disorder
Pregnancy	Suspected or confirmed pregnancy

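### New patients are risk-stratified before suitability and consent are settled, whereas controls entered without regard to risk, so entry can depend on the stratum in the new cohort only

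*Protocol article*

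**What the plan says.** The section on patient recruitment, consent and allocation gives a different sequence for each cohort.

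**New patients.** "On the initial screening day, the ‘STarT Back’ screening tool will be administered and patients stratified according to their level of risk". Routine clinical assessment is described next, and then: "Following the clinical assessment, if patients are deemed suitable for the study, a full explanation will be given by the principle investigator". Consent comes last: "If the patient is then willing to participate, written consent will be obtained". No blinding to the risk group is stated at any of these steps.

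**Historical controls** (text after Figure 1). "In the control group, risk stratification was performed by an independent party (administrator at the clinic) after the initial assessment". "The therapists were blinded as to the risk stratification of each patient until completion of the treatment intervention at three months". Entry to the programme did not depend on risk: "Following initial assessment if patients were deemed suitable, all patients irrespective of their risk stratification were entered into a generic 12 week" group programme. Consent to use their data was obtained retrospectively.

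Under Hypotheses, the cohorts are compared within risk strata: superiority for high risk, and outcomes as good as control for medium and low risk. Under Analyses, the main model is ANCOVA with baseline measures as covariate and treatment group as factor. Study design concedes a general risk of selection bias. Its safeguards are the same population, referral sources, referral criteria, setting, assessments and endpoints.

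**The concern.** In the new cohort the risk group, and so the programme, is fixed before it is settled who takes part. In the control cohort the risk group was derived separately and played no part in entry. The same stratum label may therefore cover differently selected patients in the two cohorts.

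There are two possible routes:

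- **Willingness.** A new patient who knows the stratum is agreeing to one class, to four exercise and education sessions, or to four sessions based on cognitive behavioural principles. Controls of every stratum faced the same generic programme. Reluctance about a particular programme can thin a stratum of the new cohort in a way that had no counterpart among controls.
- **Suitability.** This decision leaves some room for judgement. One exclusion in Table 1, "psychiatric illness or personality disorder", lies near the features that define high risk.

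Both hypotheses rest on within-stratum contrasts, so selection of this kind acts directly on the main results. Baseline RMDQ does not measure willingness to accept a given programme.

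**Working it through.** **Step 1: the two sequences side by side.**

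| Step | New cohort | Historical controls |
|---|---|---|
| Risk group derived | On the screening day, described before clinical assessment | After initial assessment, by an administrator |
| Therapists blind to risk group | Not stated | Yes, until three months |
| Suitability decision | After stratification and assessment | After assessment, blind to risk group |
| Programme on offer | One of three, set by stratum | One generic programme |
| Consent | Written, after the steps above | Retrospective |

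Only in the new cohort can the stratum affect entry to the programme. Retrospective consent is a separate possible selection step among controls.

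**Step 2: do the existing safeguards cover this?** The measures listed under Study design concern where patients come from and how they are treated and measured. None concerns who enters each stratum once risk is known. Baseline adjustment removes only what the baseline scores explain.

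**Step 3: the plan's own figure.** Inputs from Sample size and statistical power: effect size 0.38, SD of change 4.7, ρ = 0.592, 80% power, two-sided 0.05.

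- ANCOVA factor: 1 − 0.592² = 0.6495.
- Two-sample t-based size: 109.68 per group. 109.68 × 0.6495 = 71.24, so 72 per group. The stated 72 reproduces.

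**Step 4: how sensitive are the comparisons?** The documents give no refusal or exclusion rates, so every shift b below is an assumption. It is the part of the difference that remains after baseline adjustment. If a fraction p is lost from one cohort only, and the adjusted outcomes of those lost would differ from the rest by g points, then b = p × g. For example, 0.10 × 3 = 0.3 and 0.20 × 4 = 0.8 RMDQ points.

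- High risk, 72 per group: SE = 4.7 × √0.6495 × √(2/72) = 0.63.
- Medium or low risk, 57 per group: SE = 4.7 × √0.6495 × √(2/57) = 0.71.
- False positive with no true effect: Φ(b/SE − 1.96) + Φ(−b/SE − 1.96).
- False non-inferiority when the truth lies at the 1.8-point margin and the shift favours the new treatment: Φ(b/SE − 1.96).

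| Assumed b (RMDQ points) | High-risk false positive (nominal 5%) | False non-inferiority (nominal 2.5%) |
|---|---|---|
| 0.25 | 6.8% | 5.4% |
| 0.5 | 12.4% | 10.5% |
| 0.75 | 22.1% | 18.3% |
| 1.0 | 35.4% | 29.1% |

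These SEs apply the ANCOVA factor to 4.7 directly, as in step 3. Suppose instead that 4.7 is strictly the SD of change and the pre and post variances are equal. The outcome SD is then 4.7/√(2 × (1 − 0.592)) = 5.20 and the high-risk SE is 5.20 × √0.6495 × √(2/72) = 0.70. At b = 0.5 the high-risk false-positive rate becomes about 11%, so the picture is unchanged.

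A shift against the new treatment would instead reduce power: with a true difference of 1.8 and b = 0.5 against it, the step 4 model with SE 0.63 gives 54%.

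**The case against.** Several objections have force.

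- **Control assessors were not blind to distress.** They were blind to the STarT Back category, but their assessment included review of the self-report questionnaires, and the control measures included a distress instrument and back beliefs. A very distressed patient could have been judged unsuitable in either cohort. This stands and weakens the suitability route. It does not touch willingness to accept an assigned programme.
- **The psychiatric exclusion is listed under past medical history.** It is not a judgement on current low mood or on the screening score, and nothing links the high-risk label to exclusion. This also stands.
- **Knowledge of the stratum is inferred.** The article does not say who scores the tool for new patients or whether the person judging suitability sees the result. Streaming is placed after assessment, and the flow chart is not available here. The inference rests on the order of steps and the absence of stated blinding.
- **Controls could presumably decline too.** Nothing says otherwise. They could not, however, decline because of a stratum-specific programme, since there was none.
- **Selection bias is already conceded.** It is, in general terms, but this mechanism is not named.

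Two stronger readings are tempting. A reader might infer that the bias must favour the new intervention, through loss of the most distressed high-risk patients and of low-risk patients who doubt a single class. The documents give no rates or reasons for non-entry, and retrospective consent may have selected the controls as well, so no direction can be claimed. A reader might also see a contradiction in the statement that controls were referred and assessed identically. That statement covers referral and the components of routine assessment only, and the same paragraph openly describes the different stratification procedure. It needs no correction.

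**Conclusion.** The concern holds as a difference in the selection process. New patients are stratified before suitability and consent are settled, with no stated blinding, while controls entered without regard to risk. This opens a route by which the stratum, and the programme it dictates, can affect entry in one cohort only. Willingness is the main channel and suitability the lesser one. The within-stratum comparisons can be biased as a result, and neither the listed safeguards nor baseline adjustment addresses this.

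Direction and size cannot be determined from the documents. The tabulated error rates show only that these comparisons are sensitive to modest residual shifts, not that such shifts occur. The conclusion assumes that the described order is the order followed and that the stratum is not withheld before suitability and consent are decided. This is worth correcting where still possible, and worth reporting in any case.

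**What to change.** **Patients still to be recruited.** In Patient recruitment, consent, allocation, record suitability against Table 1 and then written consent, with all three programmes explained, before the administrator scores the tool and releases the stratum for streaming. Scoring by the administrator after assessment follows the control procedure. Prospective consent before scoring does not, because control consent was retrospective. The change reorders steps and needs no new staff. The small cost is that some patients may withdraw on learning their programme. They stay in the intention-to-treat set, but their outcomes may be missing. Recruitment was due to close in June 2013 and the article is dated December 2013, so this may help few patients or none.

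**Patients already recruited.** Tabulate those assessed but not entered, by stratum and reason, in both cohorts as far as records allow, and include controls who did not give retrospective consent. State who judged suitability in the new cohort and whether they knew the risk group. The control table may be incomplete, since nothing says that non-entered controls were scored.

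**Text.** Name this difference among the selection-bias risks under Study design.

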**Figure 1 F1:**
[figure not shown]
Study flow chart.

The historical control consists of patients who attended the Back Pain Clinic between 2009–2011. These patients were referred from the 10 GP practices and their associated physiotherapy services within the Waterford City Primary Care area in exactly the same manner as the intervention group. The patients completed a copy of the same self report questionnaires as the intervention group. In the control group, risk stratification was performed by an independent party (administrator at the clinic) after the initial assessment using the STarT Back scoring algorithm. The therapists were blinded as to the risk stratification of each patient until completion of the treatment intervention at three months. Patients in the historical control group were assessed as routine care which included history taking, a physical examination, review of completed self report questionnaires and performance of timed functional outcome measures in exactly the same manner as the intervention group. Following initial assessment if patients were deemed suitable, all patients irrespective of their risk stratification were entered into a generic 12 week group exercise/education intervention. Consent was obtained retrospectively for the inclusion of these historical controls in line with the National Consent Policy [27].

### Eligibility criteria

Patients (male and female) with chronic non specific LBP of more than three months duration and aged 18–65 years will be included. Full details of inclusion/exclusion criteria are summarised in Table 1.

**Table 1 T1:** Study inclusion and exclusion criteria

**Criteria**	
**Inclusion**	
Age	18–65 years
Diagnosis	Mechanical low back pain
Duration	Greater than 3 months duration
Language	English speaking and English literate
Consent	Willing and able to give full consent
**Exclusion**	
Pathology	Suspected or confirmed serious spinal pathology (cauda equine syndrome, fracture, metastatic, inflammatory spinal disease, pre-existing neurological condition)
Past medical history	Illicit drug use, spinal surgery, spinal cord stimulator implantation, cardiac history, psychiatric illness or personality disorder, intellectual disorder
Pregnancy	Suspected or confirmed pregnancy

### Ethical approval

Ethical approval was obtained from Waterford Regional Hospital Ethics committee Health Service Executive (HSE) South in June 2011.

### Screening tool

The STarT Back Prognostic screening Tool allows clinicians to stratify patients based on the presence of potentially modifiable physical and psychological prognostic indicators for persistent disabling symptoms [28]. Patients are stratified into one of three categories: ‘low risk’, ‘medium risk’ or ‘high risk’ of persisting symptoms. The tool consists of 9 items and includes constructs on referred pain, co-morbid pain, disability (2 items), bothersomeness, catastrophising, fear, anxiety and depression. Questions 5–9 encapsulate psychosocial features associated with persistent LBP (psychosocial subscale). The maximum score is 9. Patients are asked to agree or disagree with statements numbered 1–8 and a score of 1 is allocated to each statement the patient agrees with. The 9th item relates to bothersomeness and a score of 1 is allocated if the patient scores either ‘very much’ or ‘extremely’. Patients are classified as low risk of persisting symptoms if they score 0–3 and high risk if scoring 4 or 5 on the psychosocial subscale. All intermediate patients are classified as medium risk. High risk patients are characterised by the presence of high levels of psychosocial prognostic factors, with or without the presence of physical factors whereas medium risk patients are characterised by the presence of physical and some psychosocial prognostic factors, but the physical features are more dominant. Treatment intervention is directed dependent on the baseline risk stratification [10]. The tool has been validated against well established questionnaires regarding disability and psychological parameters and it psychometric performance was shown to be similar to that of the longer Orebro Musculoskeletal Screening Questionnaire [15,29].

### Treatment interventions

Following assessment patients will be streamed into one of three treatment interventions based on the STarT Back tool. All interventions will be grouped based and delivered by physiotherapists employed in the Back Screening Clinic.

#### Low risk intervention

Patients will attend a single 1.5 hour small group session delivered by the physiotherapist promoting active management of their back symptoms and outlining positive messages on maintaining a healthy spine in line with the ‘The Back Book’ [30]. This session will be conducted within a biopsychosocial framework and it’s aim will be to normalise the episode of LBP in line with the guidelines [2]. The benefits of exercise will be emphasised, advice to increase activity levels will be given and information on local exercise centres will be provided. Patients will be instructed with an exercise regime and given a manual which contains information on LBP management, the back exercises and a home exercise log. Each group will consist of three to five patients. The class will also offer the opportunity for patients to ask questions regarding their LBP and self-management. Patients will be encouraged to become more active in their lifestyles and to perform the back exercises on a regular basis.

#### Medium risk intervention

Patients in this group present with predominantly physical prognostic indicators (disabling LBP, referred leg pain and co-morbid pain) without high levels of psychosocial distress. Patients will attend four 90-minute group exercise/education sessions over four weeks. The content of the educational sessions will include positive messages on managing LBP based on ‘The Back Book’ [30], discussion on the benefits of exercise, a review of spinal anatomy, direction on lifting and handling, ergonomic advice, weight management and the impact of stress, anxiety and low mood on LBP. These sessions will be conducted with a biopsychosocial framework. Patients will be instructed with a stability exercise programme. Each class is a progression from the previous one. All patients will receive a ‘programme’ manual containing general educational information, instruction in each exercise and a home exercise log. Patients will be encouraged to perform the exercises independently at home at least four times/week and to complete the exercise log. Patients will also be encouraged to become more active in their lifestyle and activities such as walking, cycling, swimming or other forms of cardiovascular exercises are encouraged and logged in the activity diaries. Each group will consist of six to ten patients. Patients will maintain the exercise regime independently at home for a further eight weeks following the classes and will subsequently be reviewed at the clinic at 12 weeks. Adherence to the progamme will be monitored by reviewing the patients exercise log weekly and class attendance.

#### High risk intervention

Patients in this group display high levels of psychosocial distress around their LBP including elements of anxiety, low mood or fear. Physiotherapists administering this component of the intervention will receive extra training in cognitive behavioural therapy (CBT). Patients will attend four 120 min group sessions. The content of this intervention is modelled on the ‘high risk’ intervention delivered in the original STarT Back Trial [10]. Sessions will utilise cognitive behavioural strategies to address unhelpful beliefs and behaviours around LBP. The CBT intervention will include discussion of the bio-psychosocial model of pain, the impact of persistent pain, goal setting based around patient’s functional and social limitations, graded activity, relaxation training, relapse management. It will give the patient’s a better understanding of how they can help themselves and will focus particularly on behaviour change. It will teach the patients to identify and change maladaptive behaviours and use cognitive techniques to identify and challenge unhelpful and unrealistic thoughts and beliefs. This will promote positive behaviour and beliefs about physical activity and avoidance behaviour. Specific psychological and practical skills to promote self management of pain will be developed. Each session will also include an exercise component similar to the medium risk intervention and each patient will receive a ‘programme’ manual containing the relevant information and exercises. Patients will be encouraged to perform the exercises independently at home at least four times per week as well as adopting CBT principles e.g. pacing and goal setting. Each group will consist of four to six patients. Patients will continue the exercise regime independently at home for 8 weeks following the classes and will be reviewed at the clinic at 12 weeks. Adherence to the programme will be monitored by reviewing the patients exercise log weekly and class attendance.

#### Best care historical control

The historical control consists of patients who attended the clinic between 2009–2011 [25]. Patients were stratified using the STarT Back screening tool but a non-targeted (‘one treatment fits all’) model of care was delivered to patients. All patients undertook the same generic 12 week group education/exercise programme promoting self management and rehabilitation. The efficacy of this intervention has been established [25] and subsequently this template was utilised to develop the medium and high risk interventions. Similar to the medium and high risk interventions, the historical control comprised two phases. In phase one, patients attended once weekly for four weeks and each class was 1.5 hours in duration. Sessions included exercise and back educational information similar to the ‘medium risk’ intervention already described. In phase two, patients continued independently with the structured home exercise programme for a further eight weeks. Each group consisted of six to ten patients. Validated self report and objective physical outcome measures monitored progress at baseline and at 12 weeks. Outcomes utilised included disability (Roland Morris Disability questionnaire (RMDQ)) [31], pain (Visual Analogue Scale (VAS)) [32], distress (Distress and Risk Assessment Method (DRAM)) [33], back beliefs (Back Beliefs Questionnaire (BBQ)) [34], Simmond’s Functional Tests [35] and lumbar flexibility [36].

### Study assessment tools

#### Baseline assessment

A schematic view of the outcome measures and assessment time lines is presented in Table 2.

**Table 2 T2:** Patient outcome measures and timelines

	**Domain**	**Outcome measures**	**Time-points**
